### 2.6. Outcomes

The primary outcomes are 0-to-100 VAS for low back and leg pain. The secondary outcomes are Oswestry Disability Index (ODI); EQ-5D; Roland-Morris Disability Questionnaire (RMDQ); Oxford Claudication Score (OCS); physical function tests, including treadmill tests, assessment of the walking duration, and distance without leg pain; radiologic testing; and adverse events. Every outcome variable will be assessed before and after treatment, and follow-up will continue for up to 6 months in all groups (Table 1).

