Zero-to-100 VAS for average low back and leg pain during last week will be assessed once a week during the participating treatments. Arithmetic mean of the peak pain and lowest pain, which the patient experienced during last week regardless of position and activity (walking/standing), will be used as the average VAS score for low back and leg pain. If the patient has pain in both legs, the scores from the more severe side will be recorded. ODI is a widely used tool for assessing the disability related to low back pain. It consists of ten dimensions, such as the pain severity, ability for self-care, lifting, walking, standing, sitting, traveling, sexual function, and sleep quality. Each dimension can have 1 to 6 scores and the ODI can be calculated through the total sum of scores multiplied by 100 and divided by the numbers of answered dimensions. In addition, individual scores of 10 items will be assessed as well. The validated Korean version of ODI will be used in this study [15]. The EQ-5D will be evaluated to assess the quality of life; it has five questions that assess the respondent's mobility, self-care, daily activities, pain, and anxiety/depression, which can have scores of 1 to 3. Patients will have a five-digit number combination, which represents the quality of life. A validated Korean EQ-5D will be used for this study [16]. RMDQ is a tool for assessing the functional status of patients with low back pain. It has 24 questions, and each has yes/no options. The RMDQ score is calculated through adding all questions that are checked as yes so that it ranges from 0 (no functional limitation) to 24 (worst condition). The validated Korean version will be used for this study [17]. The OCS is a tool for evaluating the claudication severity and leg symptoms, which are the most bothersome problems for the patients with LSS. Ten questions related to three dimensions, including pain, ischemic symptoms, and physical symptoms, can have a score of zero (no symptoms) to 5 (worst symptoms), and they can be presented with the percentage of the possible maximum score. Because the RMDQ does not have validated Korean version, we will use a tentatively translated version [18]. To assess the physical function of the patients, the treadmill and walking tests will be evaluated. In this treadmill test, patients walk on a flat treadmill at a speed of 1.5 miles/sec until they complain of leg pain. For the walking test, patients will be ordered to walk on a 50 m flat track at a comfortable pace, and the time until leg pain starts will be recorded. Radiologic testing, including L-spine MRI and X-ray flexion and extension views, will be conducted to evaluate the condition of the spinal canal with stenosis and lumbar spine instability. For patients with spondylolisthesis, changes in the spinal instability will be evaluated. In addition, the AP diameters between pre- and posttreatment will be evaluated to check on the structural changes. The types and frequency of additional treatments usage during follow-up period will be assessed and analyzed after the end of the study. Adverse events (AEs) related to treatments will be monitored by the physicians, and patients should report any unexpected signs or symptoms during the treatment. AEs will be appraised using Spilker's classification, and the types and frequency will be analyzed. Outcome assessors will be open to the allocation results of the participants.

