### 2.8. Statistical Analysis

Statistical analysis will be conducted on the basis of intention-to-treat analysis (ITT). Missing values will be imputed by the last observation carried forward (LOCF) method. Baseline characteristics will be presented as the mean and standard deviation (SD) for continuous outcomes and as the frequency for categorical outcomes. Statistical analysis between groups will be conducted with a *t*-test (Wilcoxon rank sum test in case of nonnormal distribution data) or a chi-square test, respectively. Primary and secondary outcomes will be analyzed with analysis of covariance (ANCOVA), with the change in the outcome scores between the groups as the dependent variable, baseline scores as a covariate, and study groups as a fixed factor. Pre- and posttreatment differences in each group will be analyzed with a *t*-test (Wilcoxon rank sum test) or a chi-square test. Repeated measures analysis of variance will be conducted to identify the trend in data. The frequency of AEs in each group will be compared using Fisher's exact test. The types of AEs will be assessed through qualitative analysis.

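### Open assessment is applied to every outcome, including MRI and X-ray measurements that could be read masked to arm and time point at clerical cost (minor)

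*Protocol article*

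**What the plan says.** Protocol article, section 2.6, closes its account of the outcomes with "Outcome assessors will be open to the allocation results of the participants". The sentence has no exception and no rationale.

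The same section states that "The primary outcomes are 0-to-100 VAS for low back and leg pain". Among the secondary outcomes it lists "physical function tests, including treadmill tests, assessment of the walking duration, and distance without leg pain; radiologic testing; and adverse events". On imaging it adds that "the AP diameters between pre- and posttreatment will be evaluated to check on the structural changes" and that "For patients with spondylolisthesis, changes in the spinal instability will be evaluated". Patients walk on the treadmill "until they complain of leg pain", and on the track "the time until leg pain starts will be recorded". The text does not say who records it.

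Section 2.8 applies one model to all of these: "Primary and secondary outcomes will be analyzed with analysis of covariance (ANCOVA", with change as the dependent variable, the baseline score as covariate and study group as fixed factor.

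Table 1 has a single row for X-ray and MRI together. It is marked for all participants at screening. At weeks 6 and 30 it carries a different symbol, whose footnote limits flexion and extension X-ray to patients with spondylolisthesis.

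**The concern.** A blanket rule treats two kinds of outcome alike. Pain, disability and quality of life come from patients who know which treatment they received, so masking staff would not remove the patient's own expectation. A measurement made on a stored image does not pass through the patient. The reader can be kept unaware of the arm, and of whether a scan was taken before or after treatment, without altering the trial.

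At stake is the between-arm comparison of structural change. Placing a caliper on a canal or grading instability involves judgement, and the study is run at the hospital whose own programme is being tested (section 2.2). A reader who knows arm and sequence may lean, without intent, towards the expected result. That would weaken the one group of efficacy outcomes that need not depend on anyone's knowledge of treatment. The trial is also meant to examine how outcome assessment works in practice, as groundwork for a full trial (section 2.1). As written, it cannot show whether masked image reading is workable.

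**Working it through.** The plan states no figure on this point, so there is none to reproduce. The check compares sections and adds some simple counting.

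**1. Does anything elsewhere soften the rule?** Three places could.
- Section 2.2 uses opaque sealed envelopes. They conceal the next assignment and do not mask later assessment.
- Section 2.9 has an independent statistician handle and analyse the data. That person is not an outcome assessor and is not described as masked.
- Section 2.7 plans a qualitative analysis of assessors' experiences. It says nothing about masking.

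None provides a masked reader. Open assessment is stated positively, so it is not a detail that an article merely leaves to a fuller document.

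**2. Which outcomes could be masked whatever the patient knows?**

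| Outcome | Source of the value | Fully maskable by masking staff? |
|---|---|---|
| VAS, ODI, EQ-5D, RMDQ, OCS | patient's report | no |
| Treadmill and track tests | patient's complaint or onset of leg pain | no; only encouragement and recording |
| Adverse events | patient report and physician appraisal | in part |
| AP diameter, instability | measurement on images | yes |

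**3. How would a reader bias enter the analysis?** Let Y0 be the baseline value, Y1 the follow-up value and G the arm indicator. Suppose the reader adds b to follow-up values in one arm only. The analysed change is

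(Y1 + b·G) − Y0 = (Y1 − Y0) + b·G.

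The group coefficient in the ANCOVA therefore shifts by exactly b. Adjustment for baseline does not remove it, and a larger sample does not shrink it. If two arms receive shifts b1 and b2, their contrast moves by b1 − b2. A shift common to both programme arms therefore cancels between them and remains only against usual care. The documents give no value for b and no SD for either measurement, so no size is put on it here.

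**4. How many patients does it touch?**
- Planned total: 3 × 12 = 36, which matches section 2.2.
- Patients with spondylolisthesis: 2 per arm (section 2.2), so 3 × 2 = 6. Only these have follow-up flexion and extension X-ray, so the instability comparison rests on about 2 patients per arm.
- AP diameter: section 2.6 plans a before-and-after comparison, but Table 1 does not make clear which patients have a repeat MRI. The number of affected pairs cannot be fixed from the document.

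**The case against.** The strongest case on the other side is that little depends on this. The trial is a feasibility pilot, its primary outcomes are patient-reported, and recruitment, dropout and compliance (section 2.7) would be the same whoever reads the images. No image reader is named, and nothing shows that any reading has been or would be biased. All of that stands and keeps the severity low. It does not justify a rule that gives up an available protection for no stated reason.

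A reader might infer more than the documents support, in four ways.

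- **That the walking tests should be masked too, at almost no cost.** The timer is not named, and the end point depends on the leg pain of a patient who knows the treatment. A masked timer would remove only encouragement and recording effects. Table 1 schedules walking duration and distance at 8 time points, up to 36 × 8 = 288 sessions, on a single-hospital inpatient unit and at later visits. Nothing shows that staff could be kept unaware cheaply.
- **That imaging and walking are the only outcomes masking could help.** Appraisal of adverse events could also be masked in part.
- **That the bias has a known size and favours the programme arms.** That direction is plausible against usual care but not demonstrated, and between the two programme arms there is no clear prediction. Any millimetre or SD value would be assumed.
- **That the questionnaires need a new completion rule.** The article does not say how they are completed, so it gives no basis for one.

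**Conclusion.** The point holds for the image measurements only. The protocol makes assessors open to allocation without exception. This covers whoever measures AP diameter and instability, if the term assessor is read to include that person, as the unqualified sentence suggests. These are named secondary outcomes, their change is compared between arms, and they can be masked whatever patients know. The exposure to reader bias is therefore avoidable.

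Severity is low. The primary VAS outcomes and the feasibility measures are untouched, the instability comparison involves about 6 patients, the number with repeat MRI is unclear, and the size of any bias cannot be derived from the document. The conclusion assumes that images are stored and can be measured after de-identification, which is ordinary for MRI and X-ray but is not spelled out.

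**What to change.** Replace the closing sentence of section 2.6 with wording such as:

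*Measurements from MRI and X-ray will be made on de-identified images presented in random order, by a reader masked to study arm and time point. Patient-reported outcomes, and the treadmill and walking tests, which end at the patient's leg pain, will be assessed with allocation known and interpreted as open assessments.*

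The cost is clerical time to remove identifiers, arm and dates from the images and to shuffle them. Sample size, arms, visits and procedures do not change, and no additional reader is needed.

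The gain is limited to the radiologic secondary outcomes. Stating in Table 1 which patients have a repeat MRI would show how many readings are involved.

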
### 2.7. Feasibility Assessment

Recruitment rate and dropout rate during the study period will be assessed for evaluating the feasibility of the study design. Reasons for the dropouts will be analyzed. Compliance to the offered treatment interventions and outcome assessment will be evaluated based on the compliance rate of participants as well as qualitative analysis on the outcome assessors' experiences. For future full-scaled RCT, we will calculate sample size based on the study result.

### 2.8. Statistical Analysis

Statistical analysis will be conducted on the basis of intention-to-treat analysis (ITT). Missing values will be imputed by the last observation carried forward (LOCF) method. Baseline characteristics will be presented as the mean and standard deviation (SD) for continuous outcomes and as the frequency for categorical outcomes. Statistical analysis between groups will be conducted with a *t*-test (Wilcoxon rank sum test in case of nonnormal distribution data) or a chi-square test, respectively. Primary and secondary outcomes will be analyzed with analysis of covariance (ANCOVA), with the change in the outcome scores between the groups as the dependent variable, baseline scores as a covariate, and study groups as a fixed factor. Pre- and posttreatment differences in each group will be analyzed with a *t*-test (Wilcoxon rank sum test) or a chi-square test. Repeated measures analysis of variance will be conducted to identify the trend in data. The frequency of AEs in each group will be compared using Fisher's exact test. The types of AEs will be assessed through qualitative analysis.

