### 2.2. Methods

This study is a corporative clinical study with Spine Center of Mokhuri Oriental Medical Hospital, Korea Institute of Oriental Medicine, and Complementary and Integrative Medicine Program of Mayo Clinic. The study design was developed through discussion among the three organizations, and the clinical study will be conducted in Mokhuri Hospital. The study protocol was approved by the Institutional Review Board of Mokhuri Hospital (MHNBH-14001). A total of 36 LSS patients with intractable symptoms that did not subside by at least three months of conventional treatment will be recruited through advertisements in newspapers and websites for these patient communities. This is a pilot study for future, full-scaled clinical trials. As a result, 12 patients will be recruited for each group without a sample size calculation for the minimum participant number according to statistical analysis of their basic information, considering possible dropouts. Because patients with both spinal stenosis and spondylolisthesis and therapeutic responses of spinal stenosis with and without spondylolisthesis are expected to differ, we will recruit 2 patients with spondylolisthesis into the 12 participants of each group to assess the difference in the clinical outcomes. The study will be conducted at the Spine Center of Mokhuri Hospital, Seoul, South Korea. In the clinical research information service (CRIS, a representative clinical trials registry platform in Korea), the protocol was registered before the first participant is included (registration number: KCT0001218). Any patients who meet the inclusion criteria and provide written informed consent for participation in the study will be randomly allocated into one of three groups, the MT 1, MT 2, or usual care groups. For sequence generation, stratified random numbers for whether the patients do or do not have spondylolisthesis will be generated using the SAS 9.2 package software. Opaque sealed envelopes will be used to conceal which group patients have been allocated to. Over a period of four weeks, each treatment will be offered in the inpatients unit. Patients will be urged to visit the research center for follow-up evaluation at three and six months after the four weeks of treatments.

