## Figures and Tables

**Table 1 tab1:** Schedule for outcome assessment.

Stage	Screening	Treatment period in the inpatient unit				Follow-up		
Weeks	0	2	3	4	5	6	18	30
0-to-100 visual analogue scales for low back and leg pain		◯	◯	◯	◯	◯	◯	◯
EQ-5D		◯	◯	◯	◯	◯	◯	◯
Oswestry Disability Index		◯	◯	◯	◯	◯	◯	◯
Roland-Morris Disability Questionnaire		◯				◯	◯	◯
Oxford Claudication Score		◯				◯	◯	◯
Walking duration and distance without pain	◯	◯	◯	◯	◯	◯	◯	◯
Radiologic test (L-spine X-ray of flexion and extension views and L-spine MRI)	◯					*⨀*		*⨀*
Adverse events		◯	◯	◯	◯	◯	◯	◯

◯: outcome variables that will be assessed in all participants; *⨀*: L-spine X-ray of flexion and extension views will only be assessed in the patients with spondylolisthesis.

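### LOCF as the only missing-data rule can bias the ANCOVA arm comparison; a likelihood-based repeated-measures model on visits already planned should replace it

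*Protocol article*

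**What the plan says.** Section 2.8 sets an intention-to-treat basis and one rule for gaps: "Missing values will be imputed by the last observation carried forward (LOCF) method". It then gives the analysis of arm differences: "Primary and secondary outcomes will be analyzed with analysis of covariance (ANCOVA"), with change as the dependent variable, baseline as covariate and group as fixed factor. A further sentence reads "Repeated measures analysis of variance will be conducted to identify the trend in data".

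On data collection, section 2.6 says "Zero-to-100 VAS for average low back and leg pain during last week will be assessed once a week during the participating treatments", and section 2.2 adds "follow-up evaluation at three and six months after the four weeks of treatments". Table 1 places the VAS, EQ-5D, ODI and walking measures at weeks 2, 3, 4, 5, 6, 18 and 30 (walking also at screening). RMDQ and the Oxford Claudication Score (OCS) are taken only at weeks 2, 6, 18 and 30.

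Section 2.9 removes from the study patients who violate the protocol or use prohibited stenosis treatments, among other reasons. Section 2.7 makes dropout a feasibility outcome and says that the full-trial sample size will be calculated from the results.

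**The concern.** LOCF gives the right mean only if patients who leave would, on average, have stayed at their last recorded score. The protocol gives reasons to doubt that. Four weeks of inpatient treatment are meant to reduce pain. The patient education list, given in the two Mokhuri arms only, warns of new symptoms in the first treatment week and has walking increase for two to three months after treatment. After week 6 the visits are 12 weeks apart, so a patient lost after week 6 keeps that score for 24 weeks.

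Missingness related to arm is also plausible. Treatment is open, assessors know the allocation, and patients who use prohibited treatments are removed. If pain is falling and one arm loses more patients early, LOCF freezes more high scores in that arm and makes it look worse. In a pilot the cost is less a false test result than a distorted effect estimate carried into the next trial.

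**Working it through.** **No stated figure to reproduce.** The plan has 12 patients per arm, 3 × 12 = 36, with no sample size calculation. It gives no VAS path, SD, correlation or dropout rate, so all of these are assumed below. Week 2 is read as baseline and week 6 as end of treatment (weeks 18 and 30 are then 3 and 6 months later).

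**Formula.** LOCF drift in an arm = sum over visits t of P(last observed at t) × (mean at t − mean at week 6). Bias in the arm difference = drift in one arm − drift in the other.

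**Scenario 1.** Both arms follow 70, 62, 55, 48, 42 (weeks 2 to 6), so the true difference is 0. Dropout is 25% v 8%, a gap of 0.17.
- All last seen at week 3: 0.17 × (62 − 42) = 3.4 points.
- Last seen evenly at weeks 2, 3, 4: 0.17 × (28 + 20 + 13)/3 = 3.5 points.
- Last seen evenly at weeks 3, 4, 5: 0.17 × (20 + 13 + 6)/3 = 2.2 points.
- All lost after week 6, with an assumed rise to 55 by week 30: 0.17 × (42 − 55) = −2.2 points at week 30.

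**Scenario 2.** Constant dropout hazard per visit, h = 1 − (1 − d)^(1/4), which is 0.0260, 0.0543 and 0.0853 for total dropout d = 10%, 20% and 30%. Path A is 70, 62, 54, 47, 40. Path B is 70, 58, 46, 38, 30. The formula gives these drifts:

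| Dropout | Path A | Path B |
|---|---|---|
| 10% | 1.85 | 2.34 |
| 20% | 3.76 | 4.75 |
| 30% | 5.73 | 7.26 |

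- Both arms on A, 10% v 30%: 5.73 − 1.85 = +3.9.
- A with 10% v B with 30% (true difference −10): 7.26 − 1.85 = +5.4.
- A v B, 20% in each: 4.75 − 3.76 = +1.0, although dropout is equal.
- A with 30% v B with 10%: 2.34 − 5.73 = −3.4.
- Flat means, 10% v 30%: 0.

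**Simulation of scenario 2** (12 per arm, SD 20, correlation 0.6, 3,000 runs). LOCF with ANCOVA is compared with a maximum-likelihood repeated-measures estimate. Dropout is either completely at random (MCAR) or dependent on the last observed score (MAR).

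| Case | LOCF bias, MCAR / MAR | Likelihood bias, MCAR / MAR |
|---|---|---|
| Both A, 10% v 30% | +3.8 / +4.4 | 0.0 / −0.2 |
| A v B, 10% v 30% | +5.4 / +6.4 | +0.1 / +0.1 |
| A v B, 20% v 20% | +0.9 / +1.1 | 0.0 / +0.1 |
| Flat, 10% v 30% | +0.1 / +1.1 | 0.0 / +0.2 |

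The Monte Carlo SE is 0.12 to 0.15. The SD of the estimate was 6.6 to 8.4 for LOCF and 7.4 to 7.8 for the likelihood model.

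**Effect on the next trial.** Required n is proportional to 1/difference². A true −10 seen as −10 + 5.4 = −4.6 multiplies n by (10/4.6)² ≈ 4.7. Seen as −10 − 3.4 = −13.4, it multiplies n by (10/13.4)² ≈ 0.56.

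**Model size.** An unstructured covariance over the six post-baseline visits has 6 × 7/2 = 21 parameters, plus 3 × 6 = 18 arm-by-visit means, on 36 patients.

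**The case against.** The strongest reply is that this is a feasibility pilot with no power claim, that every size above is assumed, and that inpatient treatment may keep dropout low. With 12 per arm, 8% v 25% is about 1 v 3 patients. At an assumed SD of 15 to 25, the difference detectable with 80% power is about 17 to 29 points, so a shift of 2 to 6 is small beside the noise. This limits the weight of the point. It does not remove it, because the estimate may be carried forward whether or not it is significant.

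Three stronger readings are tempting, and none is supported.
- A reader might infer that LOCF biases the result whenever dropout differs by arm. Unequal dropout is not sufficient: flat means with MCAR dropout give no bias. Nor is it necessary: equal 20% dropout gives about 1 point when the paths differ.
- A reader might infer that LOCF makes the SEs and SDs badly wrong. A rerun of scenario 1 (SD 25, AR(1) correlation 0.6, last seen at weeks 2 to 4, 6,000 runs) gave a bias of +3.4, an empirical SD of 10.7 against a mean model SE of 10.6, and 93.9% interval coverage. The SD of change was 32.2, against 32.9 with complete data. The harm there is to the estimate, not to its stated precision.
- A reader might blame the repeated-measures ANOVA. Section 2.8 assigns the arm comparison to ANCOVA and uses the repeated-measures analysis only for trend. Any correction for unequal correlation is a detail an unseen analysis plan may hold.

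A mixed model also has a price: it assumes missing at random, and an unstructured version is heavy for 36 patients.

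**Conclusion.** The concern holds in a limited form. LOCF is a stated rule for every outcome, not a detail left to another document, and it can bias the ANCOVA arm difference when mean pain changes after dropout and either dropout or the paths differ by arm. Under the assumed improving paths with 8% v 25% or 10% v 30% dropout, the week-6 shift is about 2 to 6 VAS points. Its direction depends on which arm loses more patients and on how pain moves afterwards. These sizes rest wholly on assumed paths, SDs, correlations and dropout rates. In the same simulations a likelihood-based model was within about 0.2 points of the truth, with similar precision, when data were missing at random. The main consequence is for the effect carried into the full-trial sample size.

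**What to change.** In section 2.8, replace both the LOCF-based ANCOVA and the repeated-measures ANOVA. Replacing only the latter would leave the primary ANCOVA with no missing-data rule.

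- **VAS, ODI, EQ-5D and walking:** one likelihood-based repeated-measures model on all observed values at weeks 3, 4, 5, 6, 18 and 30, with arm, visit, arm × visit, baseline and spondylolisthesis stratum. Use REML and Kenward-Roger degrees of freedom. Prespecify a parsimonious covariance suited to 36 patients and unequal visit spacing, such as a random intercept with spatial-power correlation. Take the week-6 contrast as primary, in line with the before-and-after-treatment hypothesis in section 2.1.
- **RMDQ and OCS:** the same model on weeks 6, 18 and 30.
- **LOCF:** at most a labelled sensitivity analysis.

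The cost is analysis wording and code; no extra data are collected. The missing-at-random assumption must be stated. For patients withdrawn under section 2.9, the text should say that the model in effect estimates what would have been seen had they stayed, and why that is acceptable on an intention-to-treat basis.

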## 2. Methods

### 2.1. Study Objectives

The purpose of this study is to assess the feasibility of RCTs on clinical effectiveness and safety of the four-week Korean integrative treatment program for severe spinal stenosis, comparing different types of Mokhuri treatment programs and the usual care in conventional medicine in inpatient units. Information related to the compliance of the study design and interventions, the implementation of outcome assessments, and the sample size calculation for the full sized RCTs will be analyzed in this study. The null hypothesis of the primary outcome is that the change of 0-to-100 visual analogue scale (VAS) for low back pain and leg pain before and after treatment will be the same in the following three patient groups: Mokhuri treatment program group 1 (MT1 group) that will be treated with herbal medication, Chuna, acupuncture, and patient education; Mokhuri treatment program group 2 (MT2 group) that will be treated with Chuna, acupuncture, and patient education; or the usual care group that will be treated with analgesics, epidural steroid injection, and physiotherapy.

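### The ANCOVA leaves out spondylolisthesis, the factor that randomisation is stratified on, and two such patients per arm give no useful precision for the outcome difference they are recruited to assess

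*Protocol article*

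**What the plan says.** Section 2.2 (Methods) gives spondylolisthesis a special place in the design. It states that "therapeutic responses of spinal stenosis with and without spondylolisthesis are expected to differ", that "stratified random numbers for whether the patients do or do not have spondylolisthesis will be generated using the SAS 9.2 package software", and that "we will recruit 2 patients with spondylolisthesis into the 12 participants of each group to assess the difference in the clinical outcomes". The trial has three arms of 12, and "12 patients will be recruited for each group without a sample size calculation".

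Section 2.8 (Statistical Analysis) names the model for primary and secondary outcomes. It is an ANCOVA on the change score, with "baseline scores as a covariate, and study groups as a fixed factor". It has no spondylolisthesis term, and the section names no subgroup or interaction analysis.

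Section 2.6 (Outcomes) and the footnote to Table 1 add one use of the subgroup: spinal instability is followed on flexion and extension X-rays in these patients. Section 2.1 sets the overall aim: "The purpose of this study is to assess the feasibility of RCTs on clinical effectiveness and safety".

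**The concern.** There are two linked problems.

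1. **Model and design do not match.** The protocol balances the arms on a factor because it expects that factor to matter, then lists a model without it. The terms are written out, so this is a stated choice and not a detail left to an analysis plan that is not shown. If spondylolisthesis shifts the outcome, the shift is counted as residual noise and the benefit of stratifying is partly lost.
2. **A stated purpose lacks the numbers to serve it.** The two patients per arm are recruited so that a difference in clinical outcomes can be assessed. With groups of this size any such estimate would be very imprecise, and nothing in Sections 2.2 or 2.8 tells the reader to treat it as descriptive.

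At stake are some precision in the arm comparisons and the risk that a comparison resting on two patients per arm is read as evidence. Neither affects safety or the feasibility aims.

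**Working it through.** **Inputs from the protocol (Section 2.2):** 3 arms × 12 = 36 patients, which agrees with the stated total; 3 × 2 = 6 with spondylolisthesis and 30 without, a share of 1/6.

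**Assumptions (not in the protocol):** two-sided alpha 0.05, 80% target power, no dropout, and a residual SD of 25 mm on the 0-to-100 VAS, varied from 20 to 30 mm.

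**A. Cost of omitting the factor**

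The ANCOVA as written has 36 − 4 = 32 residual degrees of freedom (intercept, baseline, two arm contrasts). Adding the factor leaves 31.

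With share p = 1/6 in every arm and a stratum shift of d mm, the omitted term adds p(1 − p)d² = (5/36)d² to the error variance. The ratio of standard errors is approximately sqrt(1 + (5/36) d²/SD²).

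| Shift d | SD 20 mm | SD 25 mm | SD 30 mm |
|---|---|---|---|
| 10 mm | 1.017 | 1.011 | 1.008 |
| 20 mm | 1.067 | 1.043 | 1.030 |
| 30 mm | 1.146 | 1.095 | 1.067 |

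For example, d = 20 and SD = 25: sqrt(1 + 0.1389 × 400/625) = sqrt(1.0889) = 1.043.

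A simulation of the three-arm ANCOVA checks the direction. It used exactly 2 and 10 patients per arm, an assumed baseline–outcome correlation of 0.5, and 20,000 runs per scenario. Shifts are in units of the within-stratum outcome SD. Power is for one arm differing by 1 SD.

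| Stratum shift | Type I error, omitted / included | Power, omitted / included |
|---|---|---|
| 0 | 0.049 / 0.049 | 0.785 / 0.784 |
| 0.5 SD | 0.045 / 0.050 | 0.77 / 0.79 |
| 0.8 SD | 0.036 / 0.049 | 0.74 / 0.79 |
| 1.5 SD | 0.016 / 0.047 | 0.61 / 0.79 |

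Omission makes the test conservative and costs power. With no stratum effect, including the term costs almost nothing.

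**B. Precision of the spondylolisthesis comparison**

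The 95% half-width is t(0.975, df) × SD × sqrt(sum of 1/n).

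- Within one arm, 2 vs 10 (df 10): 2.228 × sqrt(1/2 + 1/10) = 1.73 SD, or 43 mm at SD 25.
- Pooled over arms, 6 vs 30 (df 34): 2.032 × sqrt(1/6 + 1/30) = 0.91 SD, or 23 mm.
- Treatment-by-stratum difference between two arms: sqrt(1/2 + 1/2 + 1/10 + 1/10) = 1.095. This gives 2.29 SD using the two arms alone (df 20), or 2.24 SD with the error pooled over three arms (df 30), which is 57 or 56 mm.

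Power from the noncentral distribution:

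| Comparison | 0.5 SD | 0.8 SD | 1 SD | Difference for 80% power |
|---|---|---|---|---|
| 2 vs 10, within an arm | 9% | 16% | 22% | 2.4 SD |
| 6 vs 30, pooled | 19% | 41% | 58% | 1.29 SD |
| Treatment by stratum, two arms | 7% | 11% | 14% | about 3.2 SD |

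At SD 25 mm, 1.29 SD is 32 mm, about a third of the scale.

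**The case against.** **The harm is small and on the safe side.** This stands. The arms are balanced on the factor by design, so leaving it out does not bias the arm comparison. A reader might infer that the omission invalidates the tests or inflates false positives; the simulation shows the reverse. In a 36-patient feasibility pilot with no sample size calculation, a loss of a few percent in precision is unlikely to change a decision.

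**The protocol does not claim that two per arm is enough.** This also stands. A reader might infer adequacy from the stated purpose, but Section 2.2 asserts no power or test, and Section 2.8 plans no subgroup analysis. A misleading subgroup conclusion is a possible misuse, not a planned one.

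**Some difference could be seen.** Pooled over arms, about 1.3 SD or more would be found with 80% power. The fair statement is that useful precision is lacking, not that no difference could ever appear.

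**The SD for the full trial.** A reader might infer that the SD carried forward will be too wide. Section 2.7 says only that the sample size will be based on the study result, without saying which SD. If the full trial has the same mix and the same unadjusted model, the unadjusted SD is the matching value. It is too wide only if the full trial adjusts for the factor; the variance would then be about 9% or 20% too large at shifts of 20 or 30 mm (1.043² and 1.095²).

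**Differing therapeutic responses may mean effect modification.** This is a fair reading of Section 2.2, and a main-effect term would not address it. It strengthens the second part of the point, because the treatment-by-stratum difference is the least precise of the comparisons that contrast patients with and without spondylolisthesis.

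What remains is that the written model contradicts the design's own rationale, and that the stated purpose of the subgroup exceeds what its size can deliver.

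**Conclusion.** The point holds as one of efficiency and wording. The ANCOVA in Section 2.8 omits the factor on which Section 2.2 stratifies and which it expects to matter. If the factor is prognostic, standard errors for arm comparisons are larger by about 1% to 10% for shifts of 10 to 30 mm at SD 25 mm (about 1% to 15% over SDs of 20 to 30 mm), with no bias and no excess of false positives. If it is not prognostic, nothing is lost either way.

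The aim of assessing an outcome difference from two patients per arm has no useful precision within an arm or for the treatment-by-stratum difference, and little when pooled.

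The half-widths in SD units depend only on the stated group sizes and on complete data with equal variances; dropout would widen them. The figures in millimetres and the standard error ratios rest on the assumed SD and shifts.

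**What to change.** - **Section 2.8:** add spondylolisthesis (yes/no) as a fixed factor in the ANCOVA for primary and secondary outcomes, beside baseline score and study group.
- **Section 2.2:** restate that patients with spondylolisthesis are included for balance and feasibility, that outcomes by spondylolisthesis will be reported descriptively, and that no subgroup or interaction conclusion will be drawn.

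The cost is 1 of 32 residual degrees of freedom and one reworded sentence. Recruitment, treatment and data collection do not change. The added term improves the precision of the arm comparison and should not be presented as a test of whether treatment effects differ by spondylolisthesis.
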